#### Inventory of connections to platform

Information about the data traffic is gathered and stored on the platform. The number of connections is recorded as well as number of page views, time spent per session, and time of the day of the connection. Furthermore, the medium used to access the content (i.e. if the content is accessed on a web browser, mobile phone, or mobile app) is also recorded.

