#### Inventory of use of devices

The number and frequency of measurements for each device will be recorded.

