#### Data analysis

Descriptive statistics of the data will be performed for all baseline characteristics and outcome measures. Groups will be compared using ANOVA-tests and χ^2^-tests (normal distribution) or Mann–Whitney *U*-tests (non-normal distribution) to analyze outcome measures. Comparisons of baseline characteristics will be done descriptively. Due to the repeated measure nature of the design (preoperative, one year postoperatively, and two years postoperatively) repeated measure ANOVA will be used to analyze weight-loss patterns between the intervention groups and over time.

SPSS v.25.0 (IBM Corp., Armonk, NY, USA) is used for statistical analysis and handling of data. Analysis will be performed using the intention-to-treat principle. A *p* value < 0.05 (two-sided) will be considered statistically significant. Subgroup analysis may help identify subgroups in which interventions work better or worse. Therefore, predetermined subgroup analysis will be performed. A subgroup analysis will be done comparing active platform or device users with inactive users to determine if activity influences outcome. Also, several age groups will be analyzed, as older patients might have a harder time working with electronical device and the online platform. Finally, a subgroup analysis will be performed comparing gender.

Substantial amounts of missing data will be handled using multiple imputations if deemed necessary.

Outcomes are planned to be published in a peer-reviewed journal upon completion of this trial.

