## Discussion

Over the last decades, a lot has changed in healthcare, from both the perspective of the patient as well as that of the healthcare professional. On the side of the healthcare professional, almost everything has been digitalized which, most of the time, makes working efficiently easier, for instance, viewing patients’ history or blood values. On the other hand, a lot has changed on the side of the patient as well. Nowadays the vast majority of patients in western countries have access to the Internet and mobile phones. This provides patients with a way to quickly find information about their health status, disease, and treatment. However, this information is not always correct and is frequently not applicable to individual patients. This can lead to misinformed patients. Making sure that patients are correctly informed is one of the most important aspects in healthcare.

A dedicated eHealth platform can aid or support communication towards patients. However, the value of eHealth is not yet established. Reviews on the efficacy of eHealth interventions for weight loss and weight loss maintenance show promising effects [20–22]. This trial is the first randomized research that evaluates the effects of different levels of eHealth compared to a control group after bariatric surgery.

Some limitations need to be addressed as well. As mentioned above, it can be expected that some patients will make use of other eHealth solutions or use self-monitoring devices of their own. This is, of course, dependent on the patients’ own desire and cannot be restricted. This can possibly lead to bias. To limit the effects of this bias, patients are asked if they made use of other support or devices other than the ones provided in this trial. On the other hand, some patients who enroll in one of the intervention groups might not make use of said intervention. Disinterest and lack of time can be reasons for this. Outside the context of this study, there will always be differences in the commitment to a follow-up program between patient.

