The success of bariatric surgery depends on motivation. An attempt to increase this motivation is to add eHealth applications and self-monitoring devices. However, study patients can experience this as mandatory which can imply a counterproductive effect on their incentive. In this respect, patients are informed very well about the voluntariness to use the devices and patient website. However, patients may lose interest after some time during the total lifespan of the study of two years. Also, another possible drawback of the use of devices can be that they generate an opposing effect on patients. The increased awareness of their weight can lead to some sort of compulsive need to keep losing more weight. We advise patients to not weigh themselves on a daily basis because natural changes in their weight can result in a false understanding of gaining weight. This drawback is, however, an important aspect of this study. If the devices turn out to give patients more negative than positive effects, this will result in valuable information.

It can be stated that during the first years after the operation weight loss is majorly depending on the procedure itself and other factors, such as patients’ adherence or physical activity, only start to play an increasingly substantial role in weight sustain and regain after the first year. Therefore, it might be interesting to extend to study span to the full follow-up period of five years after the initial two-year study span.

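### Comparing active with inactive users cannot show whether activity influences outcome, because use is a voluntary post-randomization state tied to motivation

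*Protocol article*

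**What the plan says.** The Data analysis section introduces the subgroup work by its purpose, "Subgroup analysis may help identify subgroups in which interventions work better or worse", and its status, "Therefore, predetermined subgroup analysis will be performed". Three analyses follow: use, age groups and gender. The first is worded: "A subgroup analysis will be done comparing active platform or device users with inactive users to determine if activity influences outcome". The main analysis is protected: "Analysis will be performed using the intention-to-treat principle".

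Use is measured during follow-up. Platform use is logged as follows: "The number of connections is recorded as well as number of page views, time spent per session, and time of the day of the connection"; for the devices, "The number and frequency of measurements for each device will be recorded".

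The Discussion bears on why patients use or do not use the intervention. It says that "some patients who enroll in one of the intervention groups might not make use of said intervention", and gives disinterest and lack of time as possible reasons. It says that patients are told use is voluntary and that interest may fade over the two years. It also says: "The success of bariatric surgery depends on motivation". Nowhere does the article caution against comparing users with non-users or name a method for a variable that arises after randomization.

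**The concern.** Age and gender are fixed before randomization, so comparing arms within those subgroups keeps the benefit of randomization. Activity is different. It is chosen by the patient after allocation, and the contrast runs between users and non-users, with the control group not named as comparator. Randomization therefore does not balance the two sides.

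The article supplies the confounding path in its own words: motivation drives the outcome, and disinterest leads to non-use. A more motivated patient may both log in more and lose more weight, even if logging in does nothing. A difference between active and inactive patients would then be read, as the plan states its purpose, as evidence that activity influences outcome.

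At stake is the interpretation of a secondary result. A null randomized comparison could stand beside a significant difference by activity, and the second could be taken as support for eHealth.

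**Working it through.** **Source of the SD and group sizes.** The plan gives no figure for this comparison. Its sample size calculation (4 BMI points, SD 8, power 0.80, two-sided alpha 0.05, two controls per experimental patient) supplies the SD and reproduces: the exact t-test power at 48 and 96 is 0.802. Allowing for 4% missing data, 48/0.96 = 50 and 96/0.96 = 100, so the total is 100 + 50 + 50 = 200. The two eHealth arms together hold 100 patients. The point below does not depend on the sample size being right.

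**Model with no effect of use.** Let motivation be a standard normal variable, correlated r1 with use and r2 with BMI reduction, with BMI SD 8 and no effect of eHealth or of use on BMI. Split patients at median use. The article gives neither the correlations nor the share of active users, so these are assumptions.

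**Expected spurious difference.** In a median split the mean of a standard normal is +0.798 in the upper half and −0.798 in the lower half. Hence

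difference = 2 × 0.798 × r1 × r2 × 8 = 12.77 × r1 × r2.

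- r1 = 0.5, r2 = 0.1: 12.77 × 0.05 = 0.64
- r1 = 0.5, r2 = 0.3: 12.77 × 0.15 = 1.92
- r1 = 0.5, r2 = 0.5: 12.77 × 0.25 = 3.19

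**Standard error.** Both arms pooled, 50 versus 50: 8 × √(1/50 + 1/50) = 1.60. One arm, 25 versus 25: 8 × √(1/25 + 1/25) = 2.26.

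**Chance of p < 0.05.** For r1 = r2 = 0.5 pooled, 3.19/1.60 = 1.99, just above the critical value of 1.96, so about 51%. Within one arm, 3.19/2.26 = 1.41, and the chance is about 29%. Simulation with two-sample t-tests gives:

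| r1 (use) | r2 (BMI) | Spurious difference, BMI points | p < 0.05, n = 100 | p < 0.05, n = 50 |
|---|---|---|---|---|
| 0 | 0 | 0.0 | 5% | 5% |
| 0.3 | 0.1 | 0.4 | 6% | 5% |
| 0.5 | 0.1 | 0.6 | 7% | 6% |
| 0.3 | 0.2 | 0.8 | 8% | 6% |
| 0.5 | 0.2 | 1.3 | 12% | 9% |
| 0.3 | 0.3 | 1.2 | 11% | 8% |
| 0.4 | 0.3 | 1.5 | 16% | 10% |
| 0.5 | 0.3 | 1.9 | 22% | 13% |
| 0.5 | 0.5 | 3.2 | 51% | 29% |

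Every difference favours active users.

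**Check on the randomized comparison.** In simulated data of the same kind, all 100 eHealth patients against 100 controls gave a mean difference of 0.0 points and p < 0.05 in about 5% of trials. The bias is confined to the comparison by activity.

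**The case against.** The strongest reply is that the harm is limited and its size unknown. This is one secondary subgroup analysis. The primary hypothesis concerns eHealth against standard care and is analysed by intention to treat. That stands.

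The reply also has support on size. The Discussion says that weight loss in the first years depends mainly on the procedure, with adherence gaining weight only after the first year. That points towards a weaker link between motivation and BMI, and so towards the upper rows of the table. The plan also does not say that the two eHealth arms would be pooled; within one arm the false-positive rate is lower. Both points stand.

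A reader might infer that the trial would probably report a false benefit of eHealth. The figures do not support this: a false significant result is the less likely outcome in all but the strongest scenario shown, and nothing in the article says the activity result would replace a null primary result. A reader might also infer reverse causation, with patients who lose weight logging in more. The article does not say so, and patients regaining weight could equally seek more content. The Discussion further presents eHealth as a way to raise motivation, so motivation may be partly a mediator.

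Finally, the threshold for active use may sit in a fuller document that is not shown. Its absence here is not a finding. But no threshold would turn this contrast into a randomized one, and the causal purpose is stated in the article itself.

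**Conclusion.** The concern holds for the stated inference. The comparison of active with inactive users is observational and confounded on the article's own account, and it cannot determine whether activity influences outcome. That conclusion needs only that motivation, or another reason for non-use, also affects weight.

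Its size rests on assumptions: SD 8, a median split, no effect of use, and correlations of 0.3 to 0.5 with use and 0.1 to 0.5 with BMI. Over that range the bias runs from negligible to a difference approaching the 4-point design effect. It does not reach the primary intention-to-treat result, and the article does not support a claim that it does. The sponsor should correct it, but it is a matter of wording and interpretation and does not threaten the trial's main answer.

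**What to change.** In Data analysis:

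- Delete the closing clause that gives the activity comparison its causal purpose.
- Separate this comparison from the age and gender subgroups, which are baseline factors.
- Describe it as an exploratory, descriptive association, with no causal claim and no significance test read as an effect of eHealth.
- State that conclusions about eHealth rest on the randomized groups.

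The usage logs are already collected, so the cost is wording. The trial gives up a causal statement about activity from this comparison, which it could not support in any case.

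A complier-average effect, with randomized arm as instrument, is an option and not a needed correction. If used, it should state its assumptions, each of which is doubtful here:

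- Control exposure may not be zero. All new patients since 2015 receive platform registration details, completing the screening questionnaire online is an inclusion criterion, and controls may use their own devices.
- The trial is open-label, so assignment may act other than through use.
- The device arm receives platform and devices together, so one instrument serves two exposures.

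It would also give wider confidence intervals.

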### Data collection

Sociodemographic and clinical information is gathered in the standard follow-up program noted in the patients’ electronic hospital files and is accessible to the treatment team. This includes: sex; age; weight; BMI; status of co-morbidities; quality of life; and blood markers. Additional parameters, such as results of questionnaires, are not normally used in the follow-up program and are therefore stored at a secured part in the Care Coordination Module functionality on the BePatient platform. To analyze the data, individuals are coded in order of registration, starting with 00–001. Members of the research team are responsible for the maintenance and monitoring of completeness and correctness of the data. An annual status report will be sent to the institutional ethical commission.

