### Statistical analysis

#### Sample size calculation

Lack of standardization for measuring the value of eHealth makes defining relevant endpoints difficult. From a clinical point of view, surgical success is defined as a total weight loss > 20%. The patients not achieving this success could especially benefit from eHealth. Furthermore, there is a group with initial weight loss and subsequent weight regain ending in the same group of failures. In a report from The Longitudinal Assessment of Bariatric Surgery Consortium, which is a multicenter observational cohort study, the results of 2458 patients were reviewed [18]. To evaluate common patterns of weight change from baseline to three years among participants following a gastric bypass, five weight-change trajectory groups were identified. A slight regain of weight occurred in every trajectory group, two years after the procedure different patterns could be distinguished. In another report, trends in weight regain following gastric bypass were reviewed (smaller group, longer follow-up) [19]. Weight gain was found to be a common complication, on average in the range of 21–29% of lost weight. Excessive weight gain was experienced by over one-third of patients. Greater initial absolute weight loss leads to more successful long-term weight outcomes. As the patterns of trajectory groups could be distinguished at two years after the operation with a difference of 10% weight loss, a hypothesis was composed. The difference of 10% corresponds to an arbitrary 4 BMI points. It is, therefore, hypothesized that the addition of eHealth would reduce the BMI by another 4 point at two years postoperatively.

This trial studies the continuous response variable BMI from independent control and experimental participants with two controls per experimental individual. If the true difference in the experimental and control means changes is 4 BMI points with a standard deviation of 8, 48 experimental individuals and 96 controls need to be studied (equal variances assumed) to be able to reject the null hypothesis that the population means of the experimental and control groups are equal with power = 0.8 and α = 0.05. In this trial, two experimental groups are defined. Therefore, at least a total of 200 patients will be enrolled in this trial, assuming no more than 4% missing data.

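### Age as an effect modifier is planned in bands; a continuous arm-by-age term would use the same data better (minor improvement to a secondary analysis)

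*Protocol article*

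**What the plan says.** The Data analysis section gives the purpose of the subgroup analyses as effect modification: "Subgroup analysis may help identify subgroups in which interventions work better or worse". It then commits to them: "Therefore, predetermined subgroup analysis will be performed". For age the form is grouping: "Also, several age groups will be analyzed, as older patients might have a harder time working with electronical device and the online platform". The article does not mention an analysis with age as a continuous variable.

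The Data collection section lists age among the routinely gathered items: "This includes: sex; age; weight; BMI". The outcome, BMI, is continuous. The significance rule for all analyses is a p "value < 0.05 (two-sided) will be considered statistically significant".

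**The concern.** The rationale is that older patients may find the technology harder. That is most simply read as a tendency that grows with age, and no threshold is offered. Banding replaces one trend contrast per arm comparison with two or three step contrasts and ignores age differences inside each band. With 50 patients per eHealth arm, three or four equal bands hold about 17 (50/3) or 12 (50/4) patients per arm.

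At stake is the chance of seeing a real decline of benefit with age. The primary comparison and the sample size are not affected.

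**Working it through.** **1. The plan's own figure.** The Sample size calculation section assumes: "If the true difference in the experimental and control means changes is 4 BMI points with a standard deviation of 8". It concludes that "48 experimental individuals and 96 controls need to be studied (equal variances assumed"), "with power = 0.8 and α = 0.05". With two controls per experimental patient, the normal approximation gives n(control) = (1 + 2) × [8 × (1.960 + 0.842) / 4]² = 94.2, that is 95 controls and 48 experimental patients. The noncentral t gives power 0.794 at 94/47 and 0.802 at 96/48, so the stated numbers reproduce. With 4% missing, 48/0.96 = 50, 96/0.96 = 100 and 192/0.96 = 200. None of this changes with the point made here.

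**2. Inputs for the interaction.**
- From the document: 96/48/48 analyzable patients, SD 8, two-sided 5%.
- Assumed, because the document gives neither: age normal with mean 43 and SD 11, cut off at 18 and 65; and the size of the interaction, taken as 1, 2 or 3 BMI points per 10 years.
- Comparison: both eHealth arms pooled (96) against control (96).

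**3. Continuous age, by hand.** Cutting the age distribution off at 18 and 65 leaves an SD of 9.94 years. The standard error of the arm-by-age slope per 10 years is 10 × (8 / 9.94) × √(1/96 + 1/96) = 8.05 × 0.144 = 1.16. The expected z is 1/1.16 = 0.86, 1.72 and 2.58 for the three interaction sizes. At a critical value of 1.96 this gives power of about 14%, 41% and 73%.

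**4. Bands, by hand, at 3 points per 10 years.** The noncentrality with continuous age is 2.58² = 6.67 on 1 degree of freedom. Under this age distribution tertiles keep about 83% of the age variance and quartiles about 89%. That leaves about 0.83 × 6.67 = 5.5 on 2 degrees of freedom (power about 53%) and 0.89 × 6.67 = 5.9 on 3 (about 50%). So the loss has two sources: less age information and more degrees of freedom for the same question. For comparison, three or four equal bands keep 79% or 86% of the variance of an untruncated normal age, and 89% or 94% of a uniform one.

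**5. Simulation of the same interaction test** (linear model; bands are tertiles, quartiles, cuts at 35/50, and cuts at 30/40/50):

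| Change per 10 years | Continuous age | Three or four bands |
|---|---|---|
| 1 BMI point | 13% | 8-10% |
| 2 BMI points | 38% | 20-25% |
| 3 BMI points | 74% | 47-54% |

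The hand calculation and the simulation agree to within a few percentage points.

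**6. How large these interactions are.** From 18 to 65 is 47 years, so the three sizes mean a swing in the treatment effect of 4.7, 9.4 and 14.1 BMI points. The hypothesized effect of the whole trial is 4 points. With a 4-point benefit at age 43, the largest scenario implies a benefit of 4 + 3 × 2.5 = 11.5 points at 18 and a disadvantage of 3 × 2.2 − 4 = 2.6 points at 65. Only the first row is near what the trial's own assumption supports, and even its swing slightly exceeds 4 points.

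**7. If the effect is a step instead.** With a 4-point step at age 50, power is about 21% with continuous age, 22-25% with bands that include a cut at 50, and 32% with a single cut at 50. Tertiles and quartiles do about as well as continuous age or slightly worse. With a 6-point step at 55, it is about 17% with continuous age, 28% with cuts at 40 and 55, and 38% with a single cut at 55.

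**The case against.** **Shape.** The rationale does not say that the effect is linear; it fits a threshold too. Step 7 shows that bands cut at a true step beat continuous age. This stands as a limit on the advice. But the article names no step, and bandings that miss it do no better than continuous age.

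**Practical gain.** At 1 point per 10 years both forms nearly always miss the interaction, and even at 2 points continuous age misses it about 62% of the time. This stands: the change improves a weak test and does not make it strong. Bands are also a familiar way to present subgroups, and the fix keeps them for that.

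**Unnamed cut points.** A reader might infer that leaving the bands unnamed contradicts the claim that the analysis is predetermined, or that the bands will be chosen after the data are seen. The document does not support this. Bands can be fixed in advance and merely summarized in an article, and boundaries are a detail commonly left to the full protocol or analysis plan, neither of which is shown. A false-positive rate of 17-18% arises only if nothing is fixed anywhere and the best of seven bandings is reported. Any one banding fixed beforehand holds about 5%.

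**Conclusion.** The point holds as a minor one. The stated choice to analyze age in bands is less efficient than a continuous term if the trend is roughly linear, and that remains true when the bands are fixed in advance. The loss is about 3 to 5 percentage points of power at 1 BMI point per 10 years, 13 to 18 at 2, and 20 to 27 at 3. The two larger losses belong to interactions bigger than the trial's 4-point effect makes plausible.

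These figures rest on an assumed age distribution, linearity, SD 8 and pooling of the eHealth arms. They say nothing against the primary analysis, and they are no evidence of inflated type I error or of bands picked after the fact.

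**What to change.** Replace the sentence on age groups with wording such as: *Effect modification by age is assessed with age in years as a continuous variable, through an arm-by-age term in the model for two-year BMI. Arm differences with 95% confidence intervals are shown at stated ages (for example 30, 45 and 60). Linearity is checked with one prespecified quadratic term. Tables by age band are descriptive.*

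The cost is a sentence or two of wording, with no new data and no change to the sample size. The price is reliance on an approximately linear trend. If the investigators have a substantive reason to expect a step at a particular age, they should state that age in advance and test it instead. In either case the report should say that power for this interaction is low.

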## Background

Bariatric surgery is the only treatment with long-standing effect on morbid obesity. The key elements to success are the patient selection, an experienced bariatric team, and a completed follow-up program. Follow-up programs can consist of, for example, providing social support in support groups, teaching psychological skills, such as coping with the body change, or teaching self-regulation of body weight [1–5]. Furthermore, follow-up is important for dietary and sports counseling [2, 5]. The experience of the team members and coaching skills are essential in indicating the suitable procedure if necessary and guiding patients through the process. Various studies have found a significant positive effect of a completed follow-up program after bariatric surgery on maintaining weight loss [6, 7]. There is a burden for this on-site provided care as organizational and financial resources are not unlimited, especially as the follow-up period is an obligatory five years or, if possible, lifelong. Even if this aftercare is provided, not all patients complete the entire program. Various reasons are possible for an increasing no-show rate; loss of enthusiasm for on-site visits could be one of them.

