## Methods/design

### Study aim

The aims of the BePatient trial are to assess the value of eHealth by comparing different levels of telehealth provided to bariatric patients. It is hypothesized that the more eHealth is provided, the higher postoperative weight loss will be, the less likely additional contacts/visits will be consumed, the higher the patients’ satisfaction will be, and the more benefits in co-morbidity will be found. The addition of eHealth provides the patients more self-control, which could result in better commitment to the follow-up program. The primary study hypothesis is that the benefit of adding eHealth to a bariatric care program would lead to a larger reduction in body mass index (BMI) two years after the procedure compared to standard care.

Two main research questions are addressed:Does an eHealth platform increase weight loss after bariatric surgery?Does providing patients with electronical wireless monitoring devices lead to more weight loss?

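### Imputing missing BMI only at discretion can turn the stated intention-to-treat analysis into a complete-case one; fix a mixed model on all randomized patients in advance

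*Protocol article*

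**What the plan says.** The Data analysis section of the protocol article states the principle: "Analysis will be performed using the intention-to-treat principle". For methods, it compares groups on outcome measures by ANOVA (or Mann-Whitney tests if the data are not normal). It adds repeated-measures ANOVA, in SPSS, on preoperative, one-year and two-year data for weight-loss patterns between groups and over time. Its one sentence on missing data is "Substantial amounts of missing data will be handled using multiple imputations if deemed necessary".

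The Sample size calculation section enrols 200 patients "assuming no more than 4% missing data".

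Three other sections bear on who is likely to be missing. The Background says not everyone completes aftercare and adds: "Various reasons are possible for an increasing no-show rate". The Study aim says eHealth gives patients more self-control, "which could result in better commitment to the follow-up program". The Discussion accepts that patients may lose interest during the two years. None of these gives a rate. The Study setting section describes the trial as open-label.

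**The concern.** The missing-data sentence rests on two judgements, whether the amount is substantial and whether imputation is necessary. Neither has a criterion, and nothing says what happens if the answer is no. The default then comes from the named procedures, and both discard incomplete patients. An ANOVA at two years loses those without a two-year BMI. Classical repeated-measures ANOVA loses anyone missing any of the three values. That is a property of the procedure, which the article does not mention. Randomized patients can thus leave an analysis described as intention-to-treat.

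Two features make this more than a matter of wording. First, the decision falls after the data are seen and without blinding, so the method could be chosen with results by arm in view. Second, if eHealth improves commitment as hypothesized, fewer patients should be lost in the eHealth arms. The Background also links completed follow-up to maintained weight loss. Loss related to both arm and weight biases a complete-case comparison of mean BMI, which is the primary outcome.

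**Working it through.** **1. The plan's own figures.** Inputs from Sample size calculation and Data analysis: "If the true difference in the experimental and control means changes is 4 BMI points with a standard deviation of 8"; two controls per experimental patient; "population means of the experimental and control groups are equal with power = 0.8 and α = 0.05"; two-sided testing ("A *p* value < 0.05 (two-sided) will be considered statistically significant").

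Power is taken from the non-central t distribution with n_E + n_C - 2 degrees of freedom and non-centrality Δ / (σ √(1/n_E + 1/n_C)).

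- 48 and 96 patients: 4 / (8 × √(1/48 + 1/96)) = 4 / (8 × 0.1768) = 2.83, giving power 0.802.
- 47 and 94 patients: power 0.794, so 48 and 96 is the smallest exact 2:1 pair that reaches 0.80.
- Allowance: 48/0.96 = 50, 96/0.96 = 100, and (48 + 48 + 96)/0.96 = 200.

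The plan's figures reproduce.

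**2. Complete-case power at other loss rates.** One experimental arm against control, 50(1 - m) against 100(1 - m), unadjusted. Every rate above 4% is an assumption, because the article gives none.

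| Loss m | Evaluable | Power |
|---|---|---|
| 0% | 50 / 100 | 0.818 |
| 4% | 48 / 96 | 0.802 |
| 5% | 47.5 / 95 | 0.798 |
| 10% | 45 / 90 | 0.776 |
| 15% | 42.5 / 85 | 0.752 |
| 20% | 40 / 80 | 0.726 |
| 30% | 35 / 70 | 0.667 |

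Power passes below 0.80 at about 5% loss (just under 6% by the normal approximation) and declines gradually. These figures are for the two-group comparison that the plan sized, not for the repeated-measures model.

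**3. Scale of bias in an assumed scenario.** Take no true effect and SD 8. Let the log-odds of a missing two-year BMI rise by 1 per SD of that BMI, with intercepts set to give 24.4% missing in controls and 11.0% in the device arm. The observed means then fall below the true mean by 1.667 and 0.794 points. The spurious difference is 1.667 - 0.794 = 0.87 points against the device arm, or 0.87/4 = 22% of the target effect. All of these inputs are assumed, and because loss depends on the unobserved value itself the scenario is missing-not-at-random.

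**4. How much a likelihood model recovers.** Use one earlier weight, observed for everyone, within the same two loss patterns.

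- Loss depends on the unobserved two-year BMI: the bias of 0.87 falls to about 0.7, 0.5 and 0.3 points when the earlier weight correlates 0.5, 0.7 and 0.85 with the two-year value.
- Loss depends on the earlier, observed weight (missing at random): complete cases are biased by about 0.44 to 0.75 points over the same correlations, and the model brings this to about zero.

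The model therefore removes the part of the bias that observed weights explain, and no more.

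**The case against.** Several stronger readings are tempting, and the article does not support them.

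- **That the plan is a complete-case analysis.** It is not fixed as one. Imputation is allowed for substantial missingness, and loss of 20% or more is what most readers would call substantial. What stands is that the choice is open, undefined and made after the data are seen.
- **That any missed visit removes a patient from the primary test.** Repeated-measures ANOVA is named for weight-loss patterns and is not designated the sole primary analysis. A two-year ANOVA loses only those without a two-year BMI. Both are still complete-case, so the point survives whichever is primary. Compounding separate losses at one and two years into a much smaller analysed fraction would need rates and a pattern of loss that the article does not give.
- **That the stated power is wrong.** The 4% is an openly stated assumption, it reproduces, and at 10% loss power is only about 2.4 points below 0.80. The Background's remark on no-shows concerns a programme running five years or longer and gives no rate. BMI is also collected in routine care. Nothing shows that 4% at two years is false.
- **That the bias is about 0.9 points.** That is an illustration with assumed inputs. With a five-point gap in loss (20% against 15%, or 10% against 5%), it is about 0.33 to 0.35 points. Its direction runs against eHealth, and the mixed model only partly corrects it.

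It can also be said that model terms and sensitivity analyses belong in a statistical analysis plan that is not shown. That is fair for the detail. But the discretionary sentence is what the article states, and such a plan would have to replace it, not merely elaborate it.

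**Conclusion.** The point holds in limited form. The stated intention-to-treat principle is not secured by the stated methods. Unless imputation is invoked under an undefined, data-dependent rule, randomized patients with missing BMI leave the analysis, in an open-label trial whose own hypothesis makes arm-related loss plausible. This rests on the wording of the Data analysis section and on how ANOVA procedures treat incomplete cases. It does not depend on any assumed loss rate.

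The size of the consequence cannot be known from the article. The assumed scenarios show complete-case bias from about a third of a BMI point to just under 0.9, against a 4-point target. The small reserve behind the 4% allowance is secondary: it is a planning assumption to justify, not an error. The change should be made before outcomes by arm are examined.

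**What to change.** Replace the discretionary sentence with a fixed rule. The primary two-year BMI comparison is a likelihood-based mixed model on all randomized patients, with baseline BMI, arm, visit and arm-by-visit, applied whatever the amount missing. If baseline BMI enters as a first outcome with a common mean across arms, patients with no postoperative weight are also retained.

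Use the routine clinic weights as further time points or auxiliary variables. The Standard care section lists visits from 1 to 24 months, and the Primary outcome measure and Data collection sections say BMI is recorded throughout follow-up and held in the hospital file. These interim weights raise the share of bias that the model can explain.

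Add one delta-adjusted sensitivity analysis, with the shift varied by arm, because the mixed model does not remove bias that depends on unobserved weight.

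In the Sample size calculation section, support the 4% from the centre's own two-year attendance, or state that unadjusted power is 0.80 up to about 4-5% loss, 0.78 at 10% and 0.73 at 20%.

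The cost is a change of wording and modest extra programming, with no new data collection. The stated power may look less favourable. The article reports the trial as still recruiting, so at that stage the change could precede any look at results.
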